### Physical performance

#### Short Physical Performance Battery

The SPPB is a broadly used test of physical performance which is validated in various patient groups [27, 28]. The SPPB assesses lower body function with three objective tests: (1) two gait speed tests using a 4-meter walk, with the fastest value for analyses, (2) five repeated chair stands without use of arms and (3) three balance tests, with side-by-side, semitandem and tandem position for 10 s each. Each test is scored from zero to four, higher scores represent better functional status. Total scores are based on the sum of these three components and ranges from zero to twelve [27, 28].

#### Six-minute walk test

A six-minute walk test (6MWT) will be used to objectively assess submaximal functional exercise capacity. The test will be performed indoors, on a walking course of 30 meters, each round representing 60 meters total. The turnaround points will be marked with tape and cones. After a period of 6 min, the distance in meters that a patient has walked will be noted. Patients choose their own walking speed and exercise intensity and if necessary stop and rest during the test [29].

#### Handgrip strength

Handgrip strength (HGS) in kilograms (kg) will be measured using a hydraulic hand dynamometer (JAMAR® 5030 J1, Sammons Preston Rolyan, Sangamon, Chicago, IL) [30]. HGS will be measured in the non-fistula or non-graft arm. Patients with central venous catheters will be measured on both sides (in case a patient will receive vascular access anytime during participation of the study) and if throughout the study the catheter stays in situ the dominant side will be used. The test is performed in sitting position, with elbow flexed at 90° and with a maximal isometric contraction. The test will be repeated and the highest of the two values will be used for analyses.

#### Physical activity

Physical activity will be assessed using the face-to-face LASA Physical Activity Questionnaire (LAPAQ). LAPAQ contains questions about the frequency and duration of several components of activity: walking, cycling, gardening, sports and household activities during the past two weeks, reported in total minutes per day [31, 32]. The total time spent on activities (in minutes) over the last two weeks will be used for analyses.

#### Physical activity monitor

Patients will be asked to wear a physical activity monitor (PAM, PAM B.V., The Netherlands) for seven days. Patients will be instructed to wear the PAM on the right hip. The PAM measures daily physical activity under free-living conditions. PAM is a small-sized and lightweight accelerometer, with a piezoelectric sensor [33]. The PAM measures acceleration in both horizontal and vertical direction and has the ability to store data continuously. The PAM provides a cumulative score, which is a measure for 24 h physical activity (i.e. the PAM score).

### Protein-energy wasting

PEW is determined by criteria which are introduced by the International Society of Renal Nutrition and Metabolism (ISRNM) in 2008 [14]. The following criteria are recommended in four domains: (1) low serum albumin, prealbumin or cholesterol, (2) low body weight, weight loss or reduced body fat, (3) reduced muscle mass, and (4) low energy or protein intake [14]. In this study, we will assess the presence of PEW for every patient according to this definition, using the presence of at least three of the following four criteria as indication of PEW: (1) serum albumin <3.8 g/100 ml, (2) BMI <23 kg/m^2^, (3) reduced MUAMC (>10% compared with the 50^th^ percentile of the reference population) and (4) protein intake <0.8 g/kg/day. We avoided time-dependent criteria for PEW in this assessment, because we are scoring the presence of PEW at short time intervals, during more than one year of follow-up. If we would include dynamic criteria, such as “weight loss over 6 months”, this would entangle the results of measurements at different moments in time and possibly obscure the effect of our treatment modalities. Apart from scoring the presence of PEW, we also will evaluate all different components of the ISRNM PEW-definition separately, in order to establish the value of the combined as well as of the individual parameters.

#### Body weight, height and body mass index

Dry body weight in kg will be used to establish weight. The patient’s nephrologist establishes the dry body weight. In case a patient does not have a dry body weight, measured weight after dialysis treatment will be noted.

Height in centimetres (cm) will be measured using knee height in patients of 55 years and older. For patients younger than 55 years height will be measured with a stadiometer. These two ways to establish height are chosen for two reasons: at first, the aspect of age-related shrinking is relevant in older patients; secondly, for calculating the height by knee height, population-specific formulas are applicable, which are only available for patients from the age of 55 years and older [34]. Knee height will be measured with a knee height calipar [Seca 207, Birmingham, United Kingdom]. For calculating BMI, current dry body weight in kg is divided by the square of height in meters.

#### Dual-energy X-ray absorptiometry

Dual-energy X-ray Absorptiometry (DXA, Hologic Discovery A (S/N84993) with software version APEX 4.5.3.) will be performed to measure total body composition. DXA will be assessed at baseline and after 12 months of follow-up. DXA provides information regarding fat mass in kg (FM), lean tissue mass in kg (LTM) and appendicular skeletal muscle mass in kg (sum of lean mass in arms and legs without bone and fat mass) [35].

#### Fat free mass and fat mass by multi-frequency bioelectrical impedance spectroscopy

Body composition will be measured with bioelectrical impedance spectroscopy (BIS), using a Body Composition Monitor (Fresenius Medical Care, Bad Homburg, Germany). Measurements will be performed at least 30 min after a patient’s haemodialysis treatment, on a mid-week dialysis day, to create optimal stability in a patient’s body fluid compartments. Shoes and socks will be removed and patients will be in supine position. Two electrodes (Fresenius Medical Care, M351431) will be placed on the dorsal surfaces of the hand and two on the foot, both on the side contralateral to the vascular access. Patients with a pacemaker will be excluded from this measurement, due to the possibility of evoking arrhythmias. Measurements will be carried out at 50 frequencies (5–1000 kHz) [36].

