## Abstract

**Background:**

Poor physical performance and protein-energy wasting (PEW) are health issues of major concern in haemodialysis patients. The conventional haemodialysis (CHD) regime, three times per week 3–5 h, is subject of discussion because of high morbidity and mortality rates. When patients switch from CHD to longer dialysis sessions, i.e. nocturnal haemodialysis (NHD), improvement in protein intake and increase in body weight is seen. However, it is unclear whether physical performance and more important aspects of PEW, such as body composition, improve as well. Therefore, the aim of this study is to investigate whether physical performance improves and PEW decreases, when patients switch from CHD to NHD. A second aim is to assess the influence of NHD on the biomarkers fibroblast growth factor-23 and sclerostin which are thought to be associated with malnutrition and mortality in patients on haemodialysis.

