## Background

Patients with end-stage renal disease (ESRD) are usually treated with a conventional haemodialysis (CHD) regimen, regularly prescribed as 3–4 times per week, 3–5 h haemodialysis sessions. However, prevalence rates of morbidity and mortality remain high, mainly due to cardiovascular complications [1–3]. Therefore, this routine of treatment is being questioned recently [3, 4].

Previous studies suggest that a twice as long haemodialysis treatment, applied as nocturnal haemodialysis (NHD), home or in-center, improves several clinical outcomes compared to CHD [5–8]. For example, improvements are found regarding hypertension and volume control, left ventricular mass, phosphate clearance, hospitalization rates, need for erythropoiesis stimulating agents and antihypertensive medications and survival [9–13]. Apart from cardiovascular complications, poor physical performance and protein-energy wasting (PEW) are risk factors of major concern in ESRD patients and contribute to this high morbidity and mortality [5–8]. Whether physical performance improves after a patient switches to NHD is unclear. Protein intake and body weight, parameters of PEW [14], seem to improve during NHD [15–17]. However, other aspects of PEW, such as muscle mass and mid-upper arm muscle circumference (MUAMC), are scarcely investigated.

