A limitation of this study is a possible negative influence of this extensive battery testing on the willingness to participate to this study: the chronic dialysis population has already the burden of a time consuming dialysis treatment combined with numerous medical appointments. For the NHD patients we expect this to be of minimal influence, because they will be motivated to observe their own progression in physical performance and nutritional status when switching to another dialysis treatment. More difficulties could arise during the recruitment of the control patients, because improvements during the year regarding their physical performance status will probably not be realized. To overcome this barrier, we want to perform as much of the assessments during dialysis, also providing patients some kind of distraction from dialysis. Not all assessments will be feasible to perform during a dialysis treatment, namely the SPPB, BIS and 6MWT. Therefore, these tests will be assessed after a patient has finished the dialysis treatment. This could be another reason for control patients to be reluctant to participate. However, the assessments are easy and quick to perform, so we will emphasize this during recruitment and thereby expect the chance of missing data to be minimized. For the NHD group all tests will be performed after their dialysis treatment, because it will be infeasible to perform these tests during NHD.

Another limitation is the lack of randomization. However, comparing different dialysis modalities is hardly possible by randomization, because patients do not want to participate in such trials. Even large study consortia do not succeed in obtaining large enough patient numbers in NHD trials [13]. To avoid differences in both groups, we will not include patients in the control group that are excluded from NHD due to medical reasons. However, there might be a difference in patients who are motivated to perform NHD in comparison to patients who do not want this treatment, i.e. selection bias. In practice we notice that reasons not to perform NHD are often social reasons, e.g. having kids or a partner and not wanting to be away during the night. However, in order to minimize the effect of bias on the study results, we will correct the results for relevant confounding factors.

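### The lean quantity named for BIS is fat free mass, which includes body water, so a lasting fluid change after the switch to NHD could be read as a change in lean tissue

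*Protocol article*

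**What the plan says.** All references are to the protocol article.

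- **BIS quantities.** The title of the BIS section reads "Fat free mass and fat mass by multi-frequency bioelectrical impedance spectroscopy". The text beneath it is more general: "Body composition will be measured with bioelectrical impedance spectroscopy (BIS), using a Body Composition Monitor". Fat free mass is the only lean-side BIS quantity named, and no hydration or fluid-corrected output is mentioned.
- **Timing of BIS.** The recording is made half an hour or more after dialysis, "on a mid-week dialysis day, to create optimal stability in" the patient's fluid compartments. The Discussion confirms the timing for SPPB, BIS and the walk test: "these tests will be assessed after a patient has finished the dialysis treatment".
- **Expected effects of NHD.** The Background says of earlier studies that "improvements are found regarding hypertension and volume control". The Abstract says that after the switch "improvement in protein intake and increase in body weight is seen". Neither gives a size.
- **Schedule (Table 1).** BIS is done at both baselines and at months 3, 6 and 12. DXA is done at the second baseline and month 12 only.
- **Other muscle measures.** The PEW score uses mid-upper arm muscle circumference (MUAMC) as its muscle criterion. DXA supplies lean tissue mass and appendicular muscle mass.

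**The concern.** The exposure under study is a longer dialysis session, and the protocol itself cites evidence that this exposure affects fluid volume. A lean measure that counts water cannot tell a change in tissue from a change in fluid. If post-dialysis fluid settles at a new level after the switch, the change occurs in the NHD group and not in patients who stay on CHD. The comparison with controls then carries it in full.

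At stake is a secondary outcome. Body composition is part of the PEW assessment, and the protocol undertakes to examine the components of the PEW definition one by one; its third and fourth domains are "3) reduced muscle mass, and (4) low energy or protein intake". BIS is the only instrumental whole-body composition measure at months 3 and 6, so DXA cannot show at those visits whether an early change in fat free mass is fluid or tissue.

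**Working it through.** **1. Do the existing safeguards remove a lasting fluid shift?**

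| Safeguard | What it handles | Lasting shift in the NHD group |
|---|---|---|
| Post-dialysis, mid-week recording | Swings within and between sessions | Remains |
| CHD control group | Changes over time common to both groups | Remains, because controls do not switch |
| Adjustment for gender, age, dialysis vintage | Baseline differences | Remains, because it arises after the switch |
| Repeated measurements in a mixed model | Random error | Remains, because repeats reduce variance and not bias |

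**2. Size of the bias.** Let L be the NHD minus CHD difference in change in lean tissue (kg), and F the same difference in excess fluid (1 L taken as 1 kg). Then

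observed difference in fat free mass = L + F.

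A fall in fluid (F < 0) hides a gain. A rise (F > 0) imitates one. If F = −L, the contrast is zero whatever the sample size.

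**3. The plan's own figure.** The plan gives no figure for BIS. Its SPPB calculation reproduces with a two-sided 5% level, 80% power and a difference of 10% of 12 points, that is 1.2:

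n = 2 × (1.960 + 0.842)² × (SD/1.2)²

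- SD 1.2: 15.7, rounded up to 16 per group.
- SD 1.5: 24.5, rounded up to 25 per group.

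This matches the stated 16–25 and is used here only to fix the two-sided 5% level and 25 per group.

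**4. Illustration for BIS.** The following are assumptions, not document figures: SD of change 1.5, 2.0 or 2.5 kg, and true lean gain L = 1.5 kg.

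SE = SD × √(2/25), giving 0.424, 0.566 and 0.707 kg. Power ≈ Φ(|L + F|/SE − 1.96).

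Example at SD 2.0 and F = −0.5: (1.5 − 0.5)/0.566 = 1.77; 1.77 − 1.96 = −0.19; Φ(−0.19) = 0.42.

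| Fluid fall | Observed difference | SD 1.5 | SD 2.0 | SD 2.5 |
|---|---|---|---|---|
| 0 kg | 1.5 kg | 94% | 76% | 56% |
| 0.5 kg | 1.0 kg | 65% | 42% | 29% |
| 1.0 kg | 0.5 kg | 22% | 14% | 11% |
| 1.5 kg | 0 kg | gain cancelled | gain cancelled | gain cancelled |

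The exact noncentral t calculation gives values lower by at most 2 percentage points.

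In the other direction, take no lean gain at all and SD 2.0. A lasting fluid rise of 0.5 or 1.0 kg gives a significant apparent gain with probability about 14% or 42%, where a correct test would give 2.5% in that direction.

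**The case against.** The strongest reply has four parts.

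**The label.** A reader might infer that fat free mass is the trial's muscle outcome. The documents do not say so. The term stands in a section title, the text speaks of body composition, and muscle is also assessed by MUAMC at every visit and by DXA at two time points. It would also be wrong to infer that BIS feeds the PEW score. This part stands, and it limits the point to one secondary measure.

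**The direction.** A reader might infer that NHD removes fluid and that the bias therefore runs against the hypothesis. Better volume control does not by itself state that residual fluid after dialysis falls. The reported weight gain does not settle the direction either, since tissue can rise while fluid falls. This part stands too: masking is possible, not shown.

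**Silence in a condensed article.** Which device output is analysed may be fixed in a fuller document. This stands only in part. The article does name a lean-side quantity, and it is one that contains water, so the comment concerns a stated choice.

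**The authors considered fluid.** They did, through the timing of the recording. That handles short-term variation but not a new steady level.

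The power figures use a simple two-group comparison and assumed inputs, whereas the plan is a mixed model. The model would change the precision, not the bias.

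**Conclusion.** The point holds as a modest improvement to a secondary outcome. Fat free mass includes body water by definition, the protocol gives its own reason to think fluid status may differ after the switch, and nothing in the design removes a lasting shift confined to one group. Each kilogram of such a shift moves the fat free mass contrast by about one kilogram, in the direction of the shift.

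How large that is in this study cannot be said: the documents give no fluid change, lean gain or SD for BIS. The fall in power from 76% to 42% or 14% rests wholly on the assumed SD of 2 kg, gain of 1.5 kg and fluid falls of 0.5 or 1.0 kg. The SPPB analysis and the PEW classification are not touched.

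**What to change.** Add one or two sentences to the BIS section:

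- Name a fluid-corrected quantity from the same recording as the BIS lean outcome: lean tissue mass excluding excess fluid, or intracellular water. The article does not state what the device reports, so first confirm that it outputs one of these.
- Report BIS fluid status by group and visit beside it.
- Keep plain fat free mass as a descriptive result.

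Fixing this in advance also prevents a choice between the two versions after the results are seen. No reanalysis of DXA is needed for this.

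**Cost.** No extra visit or test, provided the device gives the output. The corrected measure depends on the device's own model and is less directly comparable with studies that report fat free mass; keeping the latter as descriptive preserves that comparison.

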#### Mid-upper arm (muscle) circumference

Mid-upper arm circumference (MUAC) indicates a patient’s muscle mass and fat mass. Measurements will be performed using plastic tape, at midpoint of the arm without the vascular access. The mid-point of the arm is halfway between the tip of the shoulder and the tip of the elbow. Next, triceps skinfold (TSF) will be measured using a skinfold caliper (Harpenden, Baty International, West Sussex, United Kingdom) and repeated twice. The mean value of these two measurements will be used for data analyses. Mid-upper arm muscle circumference (MUAMC) is calculated by the equation: MUAMC (cm) = MUAC (cm) − (3.14 × TSF (cm)). These values will be compared to reference values by Frisancho [37].

#### Subjective global assessment

The 7-point Subjective Global Assessment (SGA) is a validated, frequently used tool and includes several components; (1) history of weight loss over the previous six months, (2) dietary intake and gastro-intestinal symptoms (appetite, vomiting, nausea and diarrhoea) and a physical examination of (3) muscle wasting and (4) loss of subcutaneous fat mass. Each of these components are scored by the executive research-dietician using a structured scoring form. In each subscale a patient will at first be classified into one of three categories (severe malnutrition, moderate malnutrition or normal nutritional status). Secondly, the score will be fine-tuned based on several aspects, e.g. how the situation was in the last two weeks. At the end a total score between 1 to 7 points will be noted. A score of 1–2 indicates severe malnutrition, 3–5 moderate malnutrition and 6–7 normal nutritional status [38, 39].

#### Dietary intake

At baseline and after 12 months of follow-up, patients will be asked to keep a 3-day dietary record on a dialysis day, a non-dialysis day and a weekend day. Patients receive instructions from the executive research-dietician how to complete their dietary record and afterwards the dietary record will be analysed by the same research-dietician. From these 3-day records a mean value will be calculated of total energy (kcal and kcal/kg), total protein (grams (g) and g/kg), fat (g), carbohydrate (g), potassium (milligrams (mg)), sodium (mg), phosphate (mg), calcium (mg), dietary fibre (g) and fluids (millilitres (ml)). Sodium intake will be considered as an estimation of true intake, because 24 h urine collection is not reliable in dialysis patients.

#### Appetite score

Visual analogue scale (VAS) for appetite will be used to establish a patient’s appetite. VAS appetite consists of a horizontal 10 centimetre line, each end of the line expressing the most negative (“I had no appetite at all”) and the most positive sensation regarding appetite (“My appetite was very good”). Patients will be asked to express their appetite during the past week by making a mark across the 10 centimetre line [40]. The VAS score is determined by measuring the distance in centimetres from the left end of the line to the point drawn by the patient. A higher score represents a better appetite.

#### Biochemical parameters

Various biochemical parameters will be assessed prior to a midweek dialysis treatment: hemoglobin (mmol/l), urea (mmol/l), creatinine (μmol/l), albumin (g/l), C-reactive Protein (mg/l), calcium (mmol/l), phosphate (mmol/l), iron saturation (%), ferritin (μg/l), parathyroid hormone (PTH, pmol/l), potassium (mmol/l), sodium (mmol/l), normalized protein nitrogen appearance (nPNA, g/kg/day) and total cholesterol (mmol/l). Standard, validated laboratory techniques are used, in order to reflect mean metabolic circumstances. Albumin will be measured before dialysis with either the bromcresol purple or green method. Bromcresol purple values will be converted to bromcresol green values using the following equation: bromcresol green = bromcresol purple + 5.5 (g/L). [41]

#### FGF-23 and sclerostin

FGF-23 levels (RU/ml) will be measured at baseline and after 6 and 12 months follow-up. Ethylenediaminetetraacetic acid (EDTA) plasma samples will be taken, using an aprotinin inhibitor to preserve stability [42]. C-terminal FGF-23 was measured using an enzyme-linked immunosorbent assay (ELISA) kit (Immunotopics, San Clemente, CA, USA). Sclerostin (pmol/l) will also be measured, at baseline and after 6 and 12 months of follow-up, using the TECO sclerostin ELISA kit (TECOmedical AG, Sissach, Switzerland). Blood samples will be collected following the patient’s dialysis treatment and will be processed by the biochemical laboratory within one hour after dialysis treatment. All blood samples will be centrifuged and stored at −80°.

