Several biomarkers have been identified as risk factors for mortality in ESRD patients. Some of them are associated with bone remodelling and could be influenced by changes in physical activity and body mass. Fibroblast growth factor-23 (FGF-23) is a phosphaturic hormone produced in the osteocytes and is found to be increased in haemodialysis patients [18, 19]. FGF-23 may be associated with low body mass index (BMI) and malnutrition [20, 21]. The protein sclerostin is an important regulator of mineralization both in bone and vasculature. Sclerostin levels increase during progression of kidney disease and in patients on dialysis; however, it is not known whether this is the result of increased sclerostin production or decreased excretion. Studies reporting on associations between sclerostin levels and survival show contradictory results [22–25]. High levels of sclerostin seem associated with higher bone mass and might also have a relation with BMI and body composition [26]. It is of interest to evaluate possible changes in FGF-23 and sclerostin concentrations between ESRD patients who switch from CHD to NHD compared to ESRD patients who remain treated with CHD.

Here, we describe the general design and methodological issues of this study. This study will examine the effects of NHD compared to CHD on multiple intermediate outcome parameters of physical performance and PEW, and on the biomarkers FGF-23 and sclerostin.

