## Methods

### Study design

This study is designed as a multicentre prospective cohort study. The NHD group will consist of patients who switch from CHD (2–4 times a week, 3–5 h) to in-centre NHD (2–4 times a week, 7–9 h). The control group will consist of patients who are treated with CHD and continue their treatment. The study protocol is in accordance with the Declaration of Helsinki and has been approved by the Medical Ethics Committee of VU University Medical Centre (VUmc).

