### Outcome parameters

The Short Physical Performance Battery (SPPB) is the primary outcome parameter. Secondary outcome parameters are PEW, FGF-23 and sclerostin. Primary and secondary outcome parameters will be measured with a variety of tests, which are listed below (Table 1). All tests will be performed by the executive research-dietician. Baseline parameters will be assessed in duplicate with a 2- to 8-week interval, and after three, six and twelve months of follow-up. The duplicate baseline measurements are done to rule out a possible “learning effect” of the physical performance tests, in this way improving the objectiveness of the results. The mean of the two baseline measurements will be used for analyses. After the baseline measurements the NHD group will switch from CHD to NHD.

**Table 1 Tab1:** Assessments of physical performance and protein-energy wasting

Assessments	Baseline 1	Baseline 2	Months 3	Months 6	Months 12
Physical performance					
Short physical performance battery	x	x	x	x	x
6- min walk test (m)	x	x	x	x	x
Handgrip strength (kg)	x	x	x	x	x
Physical activity questionnaire	x	x	x	x	x
Physical activity monitor	x	x	x	x	x
PEW					
Body weight (kg) and body mass index (kg/m^2^)	x	x	x	x	x
Dual-Energy X-ray Absorptiometry	-	x	-	-	x
Bioelectrical impedance spectroscopy	x	x	x	x	x
Mid-upper arm muscle circumference (cm)	x	x	x	x	x
Subjective global assessment (score 1–7)	x	x	x	x	x
Dietary intake	-	x	-	-	x
Visual Analogue Scale appetite (cm)	x	x	x	x	x
Other					
Laboratory measurements (e.g. albumin, C-reactive protein)	x	x	x	x	x
FGF-23 and sclerostin	-	x	-	x	x
Quality of life (KDQOL-SF)	x	x	x	x	x
Sleeping behaviour questionnaire	x	x	x	x	x

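### FGF-23 and sclerostin are sampled after dialysis, so any change in concentration within a session, of unknown size and direction and possibly zero, enters the NHD–CHD comparison

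*Protocol article*

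**What the plan says.** The Methods section on FGF-23 and sclerostin sets the sampling rule for both markers: "Blood samples will be collected following the patient’s dialysis treatment", with laboratory processing no later than one hour after the session ends. The time points are baseline, 6 and 12 months ("FGF-23 levels (RU/ml) will be measured at baseline and after 6 and 12 months follow-up"), and Table 1 places the baseline sample at the second baseline visit.

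The section on biochemical parameters uses the opposite timing for the other laboratory values: "Various biochemical parameters will be assessed prior to a midweek dialysis treatment". It adds a stated purpose: "Standard, validated laboratory techniques are used, in order to reflect mean metabolic circumstances". The biomarker section gives no reason for sampling after the session, no paired sample before it, and no midweek condition.

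The study design section defines the exposed group as "patients who switch from CHD (2–4 times a week, 3–5 h) to in-centre NHD (2–4 times a week, 7–9 h". The section on outcome parameters fixes the order: "After the baseline measurements the NHD group will switch from CHD to NHD". It also lists FGF-23 and sclerostin as secondary outcomes, and the abstract makes the influence of NHD on them the second aim.

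The Background says of the raised sclerostin levels seen in kidney disease and on dialysis that "it is not known whether this is the result of increased sclerostin production or decreased excretion".

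**The concern.** A post-dialysis concentration can depend on the session that has just ended, through removal of the marker and through fluid removal. The length of that session is the exposure under comparison. The measurement condition therefore changes together with the exposure, in one group only and only after baseline.

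At stake is how the second aim can be read. If the NHD group shows a different month 6 or month 12 value, the data cannot say whether the prevailing level has changed or whether the sample merely follows a longer session.

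**Working it through.** **1. Sampling condition by group and visit**

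| Group | Baseline 2 | Month 6 | Month 12 |
|---|---|---|---|
| NHD | after 3–5 h | after 7–9 h | after 7–9 h |
| CHD control | after 3–5 h | after 3–5 h | after 3–5 h |

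If a session multiplies the concentration by a factor that depends on its length, that factor is common to both groups at baseline and differs between them later. It remains in the within-NHD change and in the between-group difference in change. Subtracting or adjusting for baseline does not remove it. The covariates named as examples in the statistical section (gender, age, dialysis vintage) do not capture it. Session length before the draw cannot serve as a covariate either: after baseline the ranges 3–5 h and 7–9 h do not overlap, so adjusting for it would adjust for the exposure itself.

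**2. The plan's own figure**

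The document gives no sample size, clearance or variance for either biomarker. Its only calculation is for the SPPB. Reading the 10% difference as 1.2 of 12 points, n per group = 2 × (1.96 + 0.84)² × SD² / 1.2², which gives 16 at SD 1.2 and 25 at SD 1.5. This matches the stated 16–25 and does not depend on the present point.

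**3. Illustration of possible size**

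Assumptions, none of them from the document:
- equal pre-dialysis levels in both groups and no lasting NHD effect;
- first-order removal at the same hourly rate in both regimens;
- no replenishment during the session and no haemoconcentration.

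Let R be the fraction removed in 4 h. Then k = −ln(1 − R)/4, and the post-dialysis ratio NHD/CHD = exp(−k × (t_NHD − t_CHD)). For 8 h against 4 h this reduces to 1 − R.

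| R per 4 h (assumed) | 8 h vs 4 h | 7 h vs 5 h | 9 h vs 3 h |
|---|---|---|---|
| 0% | 0% | 0% | 0% |
| 10% | 10% lower | 5.1% lower | 14.6% lower |
| 20% | 20% lower | 10.6% lower | 28.4% lower |
| 30% | 30% lower | 16.3% lower | 41.4% lower |

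**4. Sensitivity to the equal-rate assumption**

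At R = 20%, 8 h against 4 h: if the NHD hourly rate is 75% of the CHD rate, the 8 h session equals 6 h of CHD removal, and the difference is 1 − 0.8^(2/4) = 10.6%. At 50% of the rate, both sessions remove the same total and the difference is zero.

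**5. Chance of p ≤ 0.05 from the artefact alone**

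With 25 per group, d = −ln(1 − R) and s the assumed SD of the log change, chance = Φ(d/(s√(2/25)) − 1.96) + Φ(−d/(s√(2/25)) − 1.96), for 8 h against 4 h.

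| R | s = 0.3 | s = 0.5 | s = 0.8 |
|---|---|---|---|
| 0% | 5% | 5% | 5% |
| 10% | 24% | 12% | 8% |
| 20% | 75% | 35% | 17% |
| 30% | 99% | 71% | 35% |

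The spread shows how much rests on inputs that the document does not give.

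**The case against.** The strongest reply is that the effect is assumed. Nothing in the document says that one session removes either marker, and at zero removal there is no artefact. The illustration also leans one way: it holds the hourly rate equal over 4 h and 8 h, lets nothing refill during the session, and ignores haemoconcentration, which could act in the other direction. All of this stands. A reader might infer that the plan will produce a false NHD reduction of 10–30%. The document does not support that, because neither the size nor the sign can be derived from it.

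A reader might also infer that pre-dialysis sampling would settle the sclerostin question raised in the Background. It would not. That passage concerns why levels rise in kidney disease and on dialysis, not removal within a session, and a lower pre-dialysis value on NHD could still reflect cumulative removal by longer sessions.

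Two further supports do not carry weight. Haemodiafiltration appears only in the eligibility criterion on prior treatment, and if its use were balanced between groups it would add noise rather than bias. No joint analysis of FGF-23 with phosphate or PTH is planned, so their different timing contradicts nothing.

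It can also be said that one sampling rule applies to both groups at every visit, and that a post-session level is a definable outcome. That is fair, but the document does not define it so, and the same rule yields different conditions once session length differs. Uncertainty about size and sign does not defend the timing either, since nothing in the document supports taking the effect as zero.

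**Conclusion.** The point holds in a limited form. Post-dialysis sampling ties the measurement condition of both biomarkers to the exposure after baseline, in the NHD group only, and the analysis cannot separate the two. This follows from the text without any assumption.

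The size is not known. Under the stated illustrative model, with 0–30% removal per 4 h, the NHD value would be 0–30% lower at 8 h than at 4 h with no lasting effect. It would be less if NHD removes more slowly per hour, and the direction is uncertain once fluid removal is considered. Confidence is high about the sampling condition and low about the magnitude.

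The consequence is confined to two secondary outcomes. The SPPB and its sample size are untouched.

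**What to change.** Take the FGF-23 and sclerostin samples in both groups from the pre-dialysis midweek draw at baseline 2, month 6 and month 12, and count the one-hour processing limit from that draw. Table 1 already schedules laboratory measurements at those visits, so the change is extra tubes at an existing draw and a reworded sampling sentence.

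The main cost is logistical. Pre-dialysis draws in the NHD group probably fall in the evening (the document gives no clock times), so processing within one hour would have to be arranged. The clock time of sampling shifts after the switch under either rule, so this does not favour post-dialysis sampling.

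If post-dialysis baselines are already stored, compare only samples taken at the same point of the session. For patients with only a post-dialysis baseline, this means that the change remains a change in post-session level.

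Where pre-dialysis sampling is not feasible, add a paired pre-dialysis sample where possible. Failing that, define the outcome as the post-session level and do not interpret a group difference as a lasting change. In every case, state that pre-dialysis sampling removes only the immediate-session component and does not distinguish production from cumulative removal.
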